## Abstract

**Background**: The majority of injuries among older adults occur due to unexpected and sudden incidents in the home environment. This study aimed to develop a protocol for the design of the health belief model-based program for preventing unintentional home injuries in older adults and to evaluate the effectiveness of the program. **Methods**: The study proposed in this protocol, Safety and Home Injury Prevention for Seniors (SHIPs), is a single-blind, parallel-group, randomized controlled trial. A total of 54 Korean older adults (≥65 years) will be randomly assigned to either (1) the intervention group (*n* = 27), which will receive the SHIPs program, or (2) the control group (*n* = 27), which will attend four lecture-only sessions. The efficacy of the program will be assessed via tests performed at baseline, 1 week after program completion, and 1 month after program completion, and analyses of the changes in injury occurrences, risk factors, preventive behaviors, beliefs about safety and injury prevention, psychological health, physiological function, and health-related quality of life. **Expected Results**: The SHIPs intervention is expected to reduce home injuries and enhance awareness and preventive behaviors among community-dwelling older adults. It may also improve their physical and psychological health and overall quality of life. **Conclusions**: The SHIPs intervention may serve as an effective community-based strategy to promote injury prevention and improve the overall well-being of older adults.

## 1. Background

Injuries among older adults are significantly associated with age-related changes in the musculoskeletal and nervous systems, underlying chronic diseases, mental health challenges, and living environments [1]. Compared to other age groups, older adults face greater exposure to risk factors owing to diminished self-protective abilities, reduced coping capacity, and delays in treatment and recovery, which increase their vulnerability to secondary injuries, disabilities, and fatalities [1,2]. These injuries significantly threaten their safety and health-related quality of life [3].

As people age, they spend more time at home, and most injuries among older adults occur unintentionally and suddenly in the home environment [4]. Preventing such unintentional home injuries requires the development and implementation of interventions that enable the recognition and management of risks in various settings. The National Council of Aging [5] recommends strategies such as fall prevention, home environment assessments, and multidisciplinary education to ensure safe daily activities, proper nutrition, medication adherence, and effective health management for older adults living at home.

Safety education for older adults should be tailored to their unique characteristics and needs. However, most safety and health programs tend to focus on school or workplace safety, offering standardized programs designed for all age groups, which fail to address the specific requirements of older adults [6]. To improve the effectiveness of safety education for seniors, it is necessary to develop standardized programs that are easy to understand, straightforward to implement, and allow for repeated practice to reinforce learning [7].

Unintentional falls are the most common type of home injury among older adults [8], with other significant causes including cuts, collisions, burns, accidents involving foreign objects or heat, and poisoning [9]. Interventions for preventing home injuries have primarily focused on fall prevention through education and exercise [10], with only a few studies addressing other frequent injury risk factors in the home environment [11]. Furthermore, home injuries among older adults result from the interplay of physical, behavioral, social, structural, and environmental factors [2,12], necessitating comprehensive, multidisciplinary prevention strategies [12].

Beliefs about home safety among older adults are shaped by their perceptions and experiences, making targeted interventions essential for fostering a sense of safety. The health belief model (HBM) provides a theoretical framework for understanding injury prevention behaviors and supporting individual-level behavior changes [13]. HBM emphasizes the crucial role of the perceptions of health and injury risks, perceived benefits of preventive actions, and personal beliefs about safety among older adults, making HBM a valuable tool for inducing positive changes in preventive behaviors [14,15]. The validity of HBM as a theoretical framework has been demonstrated in previous studies on fall prevention interventions for older adults [16,17]. Program elements in this proposed study, such as video-based lectures and peer discussion sessions, aim to influence individual beliefs and indirectly foster positive changes in safety behaviors [14,18]. In addition, exercises and hands-on practice can serve as an effective educational method by allowing participants to directly experience, practice, and acquire specific coping skills, thereby enhancing their self-efficacy [19].

This study aimed to develop a protocol for the design of an HBM-based program to prevent unintentional home injuries in older adults. The program focuses on six key areas of home injury prevention and management: falls, cuts and collisions, burns and fires, swallowing disorders, medication management, and dehydration/heat-related illnesses. The program, termed “Safety and Home Injury Prevention Program for Seniors” (SHIPs), is designed to motivate older adults to adopt home safety and prevention behaviors, empower older adults to identify risk factors, and implement preventive actions, ultimately reducing injury occurrences. In addition, the program is designed to enhance psychological health, physical function, and quality of life, all of which may be adversely affected by injury incidents [20]. Furthermore, the protocol aimed to assess the feasibility of implementing the program before pursuing additional funding for a randomized controlled trial. The findings of this study are expected to provide practical guidelines for educators involved in injury prevention initiatives.

### 1.1. Aims

#### 1.1.1. Primary Objectives

To evaluate the effectiveness of a Health Belief Model (HBM)-based health education program on the number of unintentional home injuries among community-dwelling older adults from baseline to post-intervention and at one-month follow-up.

#### 1.1.2. Secondary Objectives

To assess changes in the Health Belief Model (HBM) constructs—including home injury risk assessment, injury prevention behaviors, and beliefs about safety and injury prevention—among community-dwelling older adults from baseline to post-intervention and at one-month follow-up.To examine the effects of the program on psychological health (depression, fear of falling), physiological function (muscle strength, timed up and go test, one-leg standing test), and health-related quality of life among community-dwelling older adults, measured at baseline, immediately after the intervention, and one month after the intervention.

### 1.2. Research Hypothesis

Participants receiving the Health Belief Model (HBM)–based health education program are expected to show a significantly greater reduction in the number of unintentional home injuries from baseline to post-intervention and at one-month follow-up compared with those receiving usual care.

## 2. Methods

### 2.1. Study Design

This protocol adheres to the guidelines outlined in the Standard Protocol Items: Recommendations for Interventional Trials (SPIRIT) [21]. The study for the efficacy analysis of the SHIPs will use a single-blinded (assessor), parallel-group, randomized controlled trial design. The protocol was registered with the Clinical Research Information Service (https://cris.nih.go.kr, accessed on 15 July 2025) (Figure 1).

### 2.2. Sampling/Participants

To recruit participants, the research objectives and eligibility criteria will be presented to administrators of senior welfare centers in the Chungcheong region of South Korea for their cooperation. Participants who agree to take part and sign the informed consent form will be included in the study. Participants will be recruited through recruitment notices posted on bulletin boards and in the community, as well as through recommendations from welfare center staff, and individuals who meet the following inclusion criteria will be invited to participate: (1) aged 65 years or older; (2) not currently receiving treatment for fractures or acute illnesses; (3) classified as “robust” or “pre-frail” (K-FRAIL ≤ 2); (4) capable of exercising independently; (5) classified as “non-dementia” based on the Mini-Cog test; (6) can communicate and cooperate during anthropometric assessments; and (7) no participation in similar programs within the past 6 months.

Eligibility screening for inclusion criteria 3 and 5 will involve administering the K- K-FRAIL scale and the Mini-Cog test. The K-FRAIL scale (Korean version of the FRAIL scale) [22] evaluates frailty levels using a simple five-item questionnaire (fatigue, resistance, ambulation, illness, and weight loss) that does not require a physical examination. Each item is rated 0 or 1 point, and total scores are interpreted as follows: 0 = robust, 1–2 = pre-frail, and 3–5 = frail. The Mini-Cog test [23] assesses cognitive function through a three-step process: three-word registration, clock drawing, and three-word recall. Participants who recall all three words or recall 1–2 words while correctly drawing the clock are classified as “non-dementia.” Those who recall 1–2 words but fail to draw the clock correctly, and those who fail to recall any words are classified as having a “positive screen” for dementia. This test is widely recognized for its simplicity and reliability in screening for cognitive impairment.

The exclusion criteria will include: individuals with pain, musculoskeletal disorders, or neurological conditions that impair balance.

### 2.3. Sample Size

Sample size calculation was performed using G*Power 3.1.9.2. (Heinrich-Heine-University, Düsseldorf, Germany) Assuming a medium effect size of 0.25 [24], an alpha level of 0.05, a target statistical power of 0.80, an intraclass correlation coefficient of 0.5 to account for the correlation between repeated measures, two groups, and three measurement timepoints, the minimum required sample size was calculated to be 44 participants (22 per group). To accommodate a potential 20% dropout rate during the intervention period, the study aims to recruit a total of 54 participants, with 27 allocated to the intervention group and 27 to the control group.

### 2.4. Recruitment

After posting recruitment notices, potential participants who express interest will be contacted via phone to confirm their willingness to participate. Information sheets will be provided either in person or via email, allowing individuals sufficient time to review the study details. The information sheet will outline the study’s purpose, program, benefits, potential risks, the right to withdraw voluntarily at any time, and assurances regarding the confidentiality of personal information. Participants will be officially registered upon submitting a signed informed consent form to the research team.

### 2.5. Randomization

Participants will be randomly assigned to (1) the intervention group, which will receive the SHIPs program comprising eight sessions of lectures, discussions, and experiential activities, or (2) the control group, which will receive four lecture-only sessions. Block randomization will be performed with a 1:1 allocation ratio (intervention: control). A statistician will input the IDs of participants who have provided informed consent into a Microsoft Excel 2016 datasheet and generate unique allocation codes to ensure concealment. Randomization sequences with mixed block sizes of four and six will then be produced using SAS version 9.2 (SAS Institute Inc., Cary, NC, USA).

Sealed envelopes containing allocation codes and names of study participants will be prepared by a statistician and placed in an opaque envelope, which will be provided to the research team. To ensure allocation concealment, a separate evaluator will open one sealed, sequentially numbered opaque envelope per participant, in the order of their arrival, to determine group assignment. The randomization list will be securely kept by the statistician, ensuring that intervention researchers remain blinded to group assignments. To further maintain blinding, separate evaluators will be assigned to assess the participants, and neither the participants nor the evaluators will be aware of the group assignments. Standardized scripts were used during recruitment and data collection to ensure consistent communication, and the intervention and control sessions were conducted separately at different sites to prevent potential information exchange or cross-group influence.

### 2.6. Development of the SHIPs Intervention

#### 2.6.1. Aims and Objectives

SHIPs aims to empower older adults to protect themselves from injury by fostering beliefs about safety and prevention while promoting preventive behavior habits. The program focuses on four important areas: HBM-based program design, promotion of actionable behavioral change, strategies for injury prevention and management, and development of standardized educational materials and manuals for injury prevention.

The program’s structure is based on the HBM [14,18], designed to motivate individuals to adopt health-promoting behaviors through four key constructs: perceived susceptibility, severity, benefits, and barriers. By incorporating these HBM concepts, the program aims to encourage participants to engage in preventive behaviors. First, it improves safety awareness and highlights participants’ vulnerability to risks (perceived susceptibility: risk factor assessment). Second, it motivates action by emphasizing the potential consequences of inaction (perceived severity: consequences of injuries and their effects on quality of life). Third, it emphasizes the advantages of taking preventive measures (perceived benefits: effectiveness of preventive activities). Finally, it addresses and mitigates obstacles (perceived barriers: barrier reduction and coping strategies) to increase the likelihood of behavior change. This program incorporates self-efficacy as an additional key construct alongside the four core HBM constructs, emphasizing the crucial role of self-belief in enabling participants to sustain preventive behaviors over the long term.

#### 2.6.2. Educational Content and Teaching Methods

The program curriculum was developed based on literature reviews and statistical data [15,25,26,27,28,29,30,31,32,33], prioritizing six important areas of prevention and management at home: fall prevention, cut and collision prevention, burn and fire prevention, swallowing disorder management, medication management, and dehydration/heat-related illness prevention. The teaching methodology was designed to account for the cognitive and social characteristics of older adults, maximizing educational effectiveness by combining lecture-based and discussion-based approaches with demonstrations and hands-on practice.

The program consists of eight sessions, each lasting 60–70 min, divided into four lecture and discussion sessions and four experiential activity sessions [19,34]. The specific details of each session are outlined in Table 1. Lecture-based teaching methods were employed to systematically and effectively deliver a large volume of educational content to multiple participants in a short period [35].

During the lecture sessions (1st, 3rd, 5th, and 7th sessions), participants first watch case-based animated videos illustrating injury mechanisms in the six focus areas, providing foundational knowledge about home safety and encouraging preventive behaviors. After the videos, presentations are used to expand on topics such as injury risk factors and coping strategies. Each lecture concludes with participants completing picture quizzes and receiving small rewards to reinforce key messages, boost motivation, and enhance learning outcomes.

In the discussion sessions (3rd, 5th, and 7th sessions), participants share their experiences with implementing preventive actions to avoid injuries. Real-life testimonials from peers are incorporated to foster self-efficacy and promote the exchange of ideas. While instructor involvement is kept to a minimum, corrective guidance on preventive behaviors is provided through questions and answers to ensure meaningful and productive discussions.

The program incorporates exercises and hands-on activities to provide participants with opportunities to learn and practice home safety, injury prevention behaviors, and coping strategies. To promote practical behavioral change, experiential activities are included in the 2nd, 4th, 6th, and 8th sessions. These sessions feature fall prevention exercises (2nd session), wound disinfection and hand hygiene practice (4th session), swallowing disorder prevention exercises and first aid training, including the Heimlich maneuver (6th session), and activities focused on proper hydration and medication management (8th session). These activities are designed to help participants apply preventive behaviors effectively in their daily lives.

The fall prevention exercises were adapted from a previous study [29] and structured into beginner and intermediate levels to encourage older adults at risk of frailty or with mild mobility restrictions. The exercises, which can be performed daily at home, include functional and chair-based exercises such as marching in place, walking between rooms, wall push-ups, leg lifting and tapping, seated walking, standing up from a chair, arm stretching, calf stretches, and hamstring stretches. Each session includes group exercises, and participants are encouraged to continue these exercises individually at home at least twice a week. A previous study [36] reported that these exercises improve mobility, walking scores, and balance confidence. Participants are asked to track their home exercises and any unintentional injuries on a sticker chart, which they submit during group training sessions for monitoring and feedback purposes.

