### 2.7. Procedures

Participants who provide consent will undergo eligibility screening, including general characteristics (age, sex, comorbidities) and the K-FRAIL and Mini-Cog tests. Thereafter, eligible participants will be assessed at baseline for demographic characteristics, number of unintentional home injuries over the past 6 months, risk factors, preventive activities, beliefs, psychological health, physical function (grip strength, timed up-and-go test, and one-leg standing test), and health-related quality of life. Randomization will be performed after the baseline assessments. The intervention will span 4 weeks, with the planned programs delivered to the intervention and control groups. Although the frequency of sessions differed between groups (twice per week for the intervention group and once per week for the control group), the total intervention period was identical (4 weeks). The higher session frequency in the intervention group reflects the inclusion of both educational and behavioral components, which required additional sessions for practice and feedback. The control group received lecture-based education only. To minimize potential attention bias associated with different contact times, both groups received comparable educational content, and follow-up monitoring was implemented at similar intervals throughout the study period. Post-intervention assessments will be conducted 1 week and 1 month after program completion at a designated location.

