#### 2.7.2. The Control Group

The control group will receive lecture-based education, using the same booklets, videos, and picture quizzes as the intervention group but without the inclusion of discussion components. Sessions will be held in senior welfare center classrooms, with no restriction on the number of participants per group. The lectures will be delivered by the researcher. Pre- and post-assessment methods and procedures will be the same as those used in the intervention group.

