Safety issues and risks affect all aspects of life, and excessive sensitivity to these risks can lead to overcompensation, unnecessary expenses, fear, and anxiety, ultimately reducing the quality of life [7,55]. In particular, excessive fear of falls—a major safety concern for older adults—can limit physical activity, resulting in declines in physical and cognitive function and reduced quality of life [55]. The proposed study aims to address these challenges by promoting appropriate safety awareness and providing effective coping strategies to reduce unnecessary fear, encourage physical activity, and achieve positive outcomes.

This study faces several challenges. This study has several limitations. First, it was conducted in a single region and included a relatively small sample of older adults in the pre-frailty stage, which may limit the generalizability of the findings to other regions or populations. Second, maintaining participant engagement throughout the eight-session program may be challenging, and there is a risk of attrition during the 1-month follow-up period. Consistent adherence to the program curriculum is essential for accurately evaluating its outcomes, underscoring the importance of fostering strong researcher-participant relationships [56]. To encourage sustained participation, the program will consider participants’ preferred times and locations, provide incentives, offer personalized feedback on the program’s benefits, and maintain regular communication through short message service reminders. Third, participants may perceive the various tools and assessments, which are essential for evaluating multiple outcomes, as burdensome. To address these concerns, trained evaluators will conduct individualized, accurate, and efficient assessments to minimize inconvenience for participants. For the primary outcome measure—the number of injury incidents—participants will be encouraged to maintain injury logs to reduce the risk of recall bias. These logs will be regularly reviewed and reinforced through researcher intervention to ensure completeness and accuracy. In addition, the relatively short follow-up period restricts the ability to evaluate the long-term effects of the intervention; therefore, future studies should include extended follow-up assessments to confirm the sustainability of the observed outcomes.

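### Section 2.5 claims blinding of participants and intervention researchers that cannot hold, so the primary injury count is unblinded self-report, with an unresolved risk that injuries are captured differently by arm, mainly at T1

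*Protocol article*

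**What the plan says.** **Blinding.** Section 2.1 describes the trial as single-blind, with the assessor as the blinded party. Section 2.5 goes further. It says the statistician's custody of the randomization list keeps intervention researchers blinded to assignment, and that "neither the participants nor the evaluators will be aware of the group assignments". The same section says "a separate evaluator will open one sealed, sequentially numbered opaque envelope per participant" to determine the group.

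**Programmes.** Sections 2.7.1 and 2.7.2 have the researcher lead the intervention lectures and discussions and also deliver the control lectures. The intervention has eight sessions with discussion, exercise and hands-on practice. The control has four lectures, "using the same booklets, videos, and picture quizzes as the intervention group but without the inclusion of discussion components". Session frequency is "twice per week for the intervention group and once per week for the control group" (section 2.7).

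**Injury recording.** Section 2.8.1 defines the primary outcome as the number of home injuries, asked at T1 and T2 for the preceding month. Section 2.6.2, which describes the SHIPs programme, says: "Participants are asked to track their home exercises and any unintentional injuries on a sticker chart, which they submit during group training sessions", and gives the purpose as "for monitoring and feedback purposes". The Discussion encourages participants, without naming an arm, to keep injury logs for the primary outcome, and adds: "These logs will be regularly reviewed and reinforced through researcher intervention to ensure completeness and accuracy". Section 2.7.2 says assessment methods are the same in both arms, and section 2.7 says follow-up monitoring was at similar intervals.

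**The concern.** The primary outcome is what participants report about themselves. Two things can then move the count apart from any real effect on injuries.

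The first is knowledge of the arm. Participants who know they attend the fuller programme, and who are taught by the researcher to prevent injuries, may report fewer. The second is intensity of recording. Participants who chart injuries as they happen and hand the chart in for feedback may report more than those asked only to recall a month.

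The two pressures pull in opposite directions, so the net bias cannot be predicted or removed afterwards. The statement in section 2.5 would also lead readers to think that the first pressure is absent.

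**Working it through.** The plan gives no figure on this point, so there is none to reproduce. The check sets the sections side by side, then adds a labelled illustration.

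**1. Can the blinding in section 2.5 hold?**
- Intervention researchers: the researcher leads the sessions in one arm and lectures in the other (2.7.1, 2.7.2). A person who runs an exercise or discussion session knows which programme it is. The claim cannot be met.
- Participants: they attend eight sessions or four, with or without discussion and practice, at different sites (2.5), after an information sheet that describes the programme (2.4). They know what they receive. At most they may not know which programme is the experimental one, and section 2.5 claims more than that.
- Evaluators: masking is feasible, and it is what section 2.1 claims. Section 2.5 uses the same word for the person who opens the envelope and for the people who assess outcomes, and does not say outright that they are different people.

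**2. Is injury recording shown to be the same in both arms?**
- Sticker chart: described only within SHIPs, on the same form as home exercises, and handed in at group training sessions. The control description has neither home exercise nor training sessions, and the materials it lists do not include the chart.
- Logs in the Discussion: not limited by arm, but with no form, collection schedule or review frequency. The text does not say whether log and chart are the same thing.
- Table 2 marks the injury count during the intervention column as well as at T0, T1 and T2, for both arms, without naming the instrument.
- Equal assessment methods (2.7.2) cover the pre- and post-assessment. An identical T1 question can still be answered differently by people who have and have not been charting.

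The text neither states unequal recording nor establishes equal recording.

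**3. Which time point is exposed?** T1 falls one week after a four-week programme and looks back one month.
- With a month of 30 days: 30/7 = 4.3 weeks; 4.3 − 1 = 3.3 programme weeks in the window.
- With a month of four weeks: 4 − 1 = 3 programme weeks.
- T2 falls one month after the end and looks back one month, so no programme weeks are in its window.

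**4. Illustration of size.** All capture shares and injury rates here are assumptions; the documents give none. If c_I and c_C are the shares of injuries recorded in the intervention and control arms, then observed rate ratio = true rate ratio × c_I / c_C.

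| c_I / c_C | True ratio 1.00 seen as | True ratio 0.70 seen as |
|---|---|---|
| 0.95 / 0.80 | 1.19 | 0.83 |
| 0.90 / 0.70 | 1.29 | 0.90 |
| 0.90 / 0.60 | 1.50 | 1.05 |
| 0.70 / 0.90 | 0.78 | 0.54 |

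If the extra capture applied only in three of four window weeks, with an even injury rate and 0.70 capture otherwise, intervention capture at T1 would be 0.75 × 0.90 + 0.25 × 0.70 = 0.85. A true 0.70 would then appear as 0.70 × 0.85/0.70 = 0.85.

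A simulation used 27 per arm, Poisson counts, no true effect, assumed rates of 0.2 to 1.0 injuries per person-month, and a two-sided 5% test on arm totals (20,000 runs). It rejected in 4.3% to 5.0% of runs with equal capture, 5.9% to 12.6% at 0.90/0.70, and 5.7% to 12.8% at 0.70/0.90. This is not the planned analysis, which is repeated-measures ANOVA or generalized estimating equations (2.9). It shows only the order of size.

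**The case against.** The strongest reply concerns ascertainment. A reader might infer that the protocol records the primary outcome differently in the two arms. The documents do not say so. The primary count is a recall question at T1 and T2, and section 2.7.2 says methods are the same. The chart serves monitoring and feedback and is not named as the source of the count. The Discussion offers logs to participants in general, and section 2.12 asks participants in general to report injuries at once. If training sessions means only the four experiential ones, charts would come in weekly, which is the control arm's own contact frequency. All of this stands, and it reduces the point to a risk. It does not remove it, because no section says that controls submit and have reviewed the same record.

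A reader might also infer that outcome assessors are unmasked because an evaluator opens envelopes. The text calls that person separate, and different people is a natural reading. Only a clarification is needed.

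On blinding, one could read the sentence about intervention researchers as concealment of the upcoming sequence. That would be a reasonable aim, but the sentence speaks of group assignments, and the claim about participants has no such reading.

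Finally, tracking injuries with feedback may be an intended part of SHIPs. If so, the record that feeds the outcome should be kept apart from it.

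**Conclusion.** The blinding point holds as a contradiction. Section 2.5 claims masking of participants and intervention researchers, which conflicts with section 2.1 and cannot be achieved with these two programmes. The primary outcome should be treated as unblinded self-report.

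The ascertainment point holds as a risk, mainly at T1. It rests on the chart being described only for SHIPs and on the absence of any statement that controls keep and submit the same record on the same schedule.

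The size cannot be fixed from the documents. Under the assumed capture shares, a true rate ratio of 0.70 could appear anywhere from 0.54 to 1.05. A prediction that the intervention arm will show too many injuries, or too few, would go beyond the text. The point deserves correction because the outcome is primary and the remedy is cheap.

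**What to change.** 1. Replace the masking wording in section 2.5 so that it agrees with section 2.1: outcome assessors are masked; participants and instructors are not; the injury count is unblinded self-report.
2. Give both arms the same dated injury log, collected and reviewed on the same weekly schedule, and state it in sections 2.6.2, 2.7.2 and 2.8.1. Name the source of the T1 and T2 count: recall, log, or recall checked against the log. The home-exercise chart can stay part of SHIPs.
3. State that anyone who opens envelopes or delivers sessions does not take the T1 or T2 count.

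The cost is one extra form for controls, minor reassignment of existing staff and a few sentences. Keeping a log may itself make controls more careful, but the Discussion already encourages logs without limit by arm. Section 3 schedules the study from 1 April 2025 to 31 January 2026. For participants already past T1, the log cannot be added, so the report should say what each arm actually kept and how it was reviewed.
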